
When considering the somewhat restricted number of clinical studies focusing on the success of internet- and smartphone-based outpatient rehabilitation management for post-PCI ACS patients, as well as the lack of large-sample, multicentre RCTs, the case sources are somewhat restricted, and the generalizability of the research findings is weak.

Therefore, the aim of this study is to conduct a multicentre RCT in China. Additionally, previous clinical assessments have primarily focused on patients' cardiac function indicators, whereby they often used the 6-minute walk distance as the main outcome measure, with limited research on clinical endpoint indicators such as major adverse cardiovascular and cerebrovascular events (MACCEs), patients' quality of life, mental health, and other cardiac function indicators (such as brain natriuretic peptide). Therefore, in this study, in addition to focusing on the 6-minute walk distance as a cardiac function indicator, we will also assess MACCEs, quality of life, and other cardiac function evaluation indicators within and between groups to better understand the impacts of digital health management on the outpatient rehabilitation effect for ACS patients who undergo PCI. These findings will provide a basis for an accessible, affordable, and scalable CR/SP model and provide the foundation for improvements in home-based rehabilitation management.

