## Sample size and statistical analyses

This study will adopt a multicentre, open-label, RCT design, with the primary endpoint being MACCEs at one year after patient discharge. The sample size will be calculated based on this primary endpoint.

The following sample size calculation formula was used:$$n=\frac{2\bar{p}\bar{q}{\left(Z_{\alpha }+Z_{\beta }\right)}^{2}}{{\left(p1-p2\right)}^{2}}$$where “*n*” represents the sample size per group, and Z*α* and Z*β* are obtained from statistical tables. When *α* = 0.05, Z_0.05_ = 1.96. For a power (test efficacy) of 0.9, Z*β* = 1.28; for a power of 0.8, *β* = 0.2, and Z*β* = 0.84. In this study, *α* = 0.05 and *β* = 0.2 were chosen; thus, Z*α* and Z*β* are 1.96 and 0.84, respectively.

“p^−^” represents the mean of p1 and p2, whereas “q^−^” represents the mean of 1-p1 and 1-p2. Additionally, p1 and p2 are the event rates for the experimental and control groups, respectively. Based on previous research (18) and clinical considerations, the one-year MACCE rate for the control group was set at 20% (p2 = 20%). After intervention, the MACCE rate in the experimental group is expected to be reduced by 30%, thus resulting in p1 = 14%.

Using these values in the formula, the required sample size per group (n) is calculated as 615, thus yielding a total sample size of 1,230. With a potential 10% dropout rate considered, the necessary total sample size for this study is 1,366, with 683 patients being allocated per group.

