### Statistical analysis

This study will use two-sided tests for the statistical analysis, with a significance threshold set at *α* = 0.05. A *p* value less than 0.05 will be regarded as being statistically significant. The principles for data description and hypothesis testing are as follows:
(1)Statistical descriptionAn analysis will be conducted on the continuous variables to ascertain if they exhibit a normal distribution. Continuous variables that follow a normal distribution will be presented as the means with standard deviations, whereas those that do not follow a normal distribution will be shown as medians with interquartile ranges.

Categorical variables will be presented as frequencies (number of cases) and percentages.
(2)Statistical inferenceFor comparisons between the groups, normally distributed continuous variables will be analysed via independent sample *t* tests. For nonnormally distributed continuous variables, comparisons will be performed via the Mann–Whitney *U* test. Within-group comparisons involving continuous variables with a normal distribution will utilize paired *t* tests, whereas those with nonnormal distributions will employ Wilcoxon rank-sum tests.

*Χ*^2^ tests, Fisher's exact tests, or nonparametric rank-sum tests will be used to compare the categorical variables.

Further analyses will include multivariate model adjustments to account for potential confounding factors and to determine the stability of the results. For comparisons of data at different time points, repeated-measures ANOVA will be used to assess between-group differences over time. Kaplan–Meier curves will be plotted to illustrate the cumulative occurrence of cardiovascular events over time, and log-rank tests will be used for comparisons. Additionally, baseline characteristics will be compared between participants who are included and not included in the final analysis to verify if the missing data are random. Cox proportional hazards models will be used to estimate the hazard ratio (HR) and 95% confidence interval (CI) for the primary endpoint.

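### The within-group test named for non-normal outcomes is the Wilcoxon rank-sum test, an independent-samples test; paired data need the signed-rank test.

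*Protocol article*

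**What the plan says.** Item (2), Statistical inference, under Statistical analysis sets four rules for continuous variables:

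- Between groups, normal: independent-samples t test.
- Between groups, non-normal: "For nonnormally distributed continuous variables, comparisons will be performed via the Mann–Whitney" U test.
- Within groups, normal: "Within-group comparisons involving continuous variables with a normal distribution will utilize paired" t tests.
- Within groups, non-normal: "whereas those with nonnormal distributions will employ Wilcoxon rank-sum tests".

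The last paragraph of the Introduction shows that within-group comparisons are intended: the trial will assess MACCEs, "quality of life, and other cardiac function evaluation indicators within and between groups". Table 5 schedules the cardiac function measures, BNP, quality of life, anxiety, depression and biochemistry at baseline and at four follow-ups on the same patients. The signed-rank test is named nowhere in the article.

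**The concern.** A within-group comparison sets two measurements on the same patient against each other. The plan recognises this for normal variables by choosing the paired t test. For non-normal variables it names a test for two independent samples, the same procedure that it uses to compare the arms. One test is therefore assigned to both unpaired and paired data.

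The null variance of the rank-sum statistic is derived for independent samples. When a patient's values at two visits are positively correlated, that variance is too large for the data, so p-values are too large and real change is missed. The rule would apply to every repeated outcome found to be non-normal. BNP, some of the biochemistry and the anxiety and depression scores are likely candidates, though which outcomes these will be is an expectation. Normal and skewed outcomes would then be judged by tests of different sensitivity, and a small change could look weaker in a skewed outcome because of the test alone.

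**Working it through.** **Inputs.** Two-sided tests at 0.05 (Statistical analysis). 615 patients per arm before dropout (Sample size and statistical analyses). The article gives no within-patient correlation, so it is assumed over 0 to 0.9. A shift of 0.1 SD on the log scale and lognormal data are also assumptions.

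**The plan's own figure.** With event rates of 14% and 20% the mean is 0.17, and the normal quantiles "are 1.96 and 0.84, respectively". The formula gives 2 × 0.17 × 0.83 × (1.96 + 0.84)² / 0.06² = 0.2822 × 7.84 / 0.0036 = 614.57, so 615 per group. Then 1,230 / 0.9 = 1366.7 against the stated 1,366, which agrees within rounding. This figure is for MACCE; it serves here only as the number of pairs.

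**True size of the rank-sum test on paired data.** Under no change, pairing shrinks the variance of the statistic by a factor of about 1 − ρ (strictly, ρ is the rank correlation). The actual two-sided error is then about 2 × [1 − Φ(1.96 / √(1 − ρ))]:

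- ρ = 0.3: 1.96 / 0.837 = 2.34, giving 1.9%
- ρ = 0.5: 1.96 / 0.707 = 2.77, giving 0.6%
- ρ = 0.7: 1.96 / 0.548 = 3.58, giving 0.03%

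**Simulation.** 615 lognormal pairs, 2,000 runs per setting. The Monte Carlo standard error at 5% is √(0.05 × 0.95 / 2000) = 0.5 percentage points.

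| Assumed ρ | Rank-sum type I error | Signed-rank type I error (raw differences) | Rank-sum power | Signed-rank power (raw differences) | Signed-rank power (log differences) |
|---|---|---|---|---|---|
| 0 | 5.2% | 4.3% | 40% | 36% | 41% |
| 0.3 | 1.7% | 5.2% | 41% | 47% | 55% |
| 0.5 | 0.9% | 5.5% | 35% | 61% | 68% |
| 0.7 | 0.15% | 5.3% | 32% | 81% | 88% |
| 0.9 | 0.0% | 5.2% | 23% | 100% | 100% |

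Power is for the 0.1 SD shift. The rank-sum test is unchanged by a log transformation and the signed-rank test is not, so both scales are shown. The plan mentions no transformation, so the raw-scale column is the fairer comparison.

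**Hand check at ρ = 0.5.** On log differences the SD of a difference is √(2 × 0.5) = 1.

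- Signed-rank: 0.1 × √615 × √(3/π) = 2.48 × 0.977 = 2.42; power ≈ Φ(2.42 − 1.96) = 68%.
- Rank-sum: 0.1 × √(615/2) × 0.977 = 1.71, with true SD 0.707; power ≈ Φ((1.71 − 1.96) / 0.707) = 36%.

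Both agree with the simulation.

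**A larger shift.** At 0.2 SD, simulated rank-sum power is about 98% (ρ = 0.5) and 99% (ρ = 0.7), against 99% and 100% for the signed-rank test on raw differences.

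**The case against.** The strongest reply is that this is a naming slip. The paragraph pairs the independent t test with Mann–Whitney and then the paired t test with a Wilcoxon test, so a reader can infer that the paired Wilcoxon test was meant. The trial's question is also untouched. The hypothesis is superiority between arms, the primary endpoint is one-year MACCE with log-rank and Cox methods, and change over time between arms is assigned to repeated-measures ANOVA. Within-arm tests do not estimate the treatment effect. The error is conservative, so it cannot create a false claim of change, and the loss of power is large only for small shifts.

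All of this stands, and it limits the importance of the point. It does not make the sentence right. An analyst who follows it runs a test whose assumption fails; one who silently corrects it departs from the published plan. Nothing else in the article resolves the matter.

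**Conclusion.** The concern holds: the named test is wrong for the data to which it is assigned. With positive within-patient correlation the rank-sum p-values are too large. At correlations of 0.3 to 0.7 a nominal 5% test operates at between 1.7% and 0.15%. For a 0.1 SD log-scale shift, the power lost against the signed-rank test on raw differences runs from 6 points (47% − 41%) to 49 points (81% − 32%). At zero correlation the two tests behave about alike. The sizes rest on the assumed correlations, the lognormal shape and the small shift; the miscalibration itself needs only positive correlation.

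The reach is narrow: within-arm p-values for non-normal continuous secondary outcomes. It should be corrected, but it does not threaten the trial's main conclusion.

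**What to change.** Under Statistical analysis, item (2), replace the rank-sum test with the Wilcoxon signed-rank test for within-group comparisons of non-normal variables, and keep Mann–Whitney U for between-group comparisons only. Check the statistical analysis plan, which is not shown here, for the same wording. Reporting the Hodges–Lehmann estimate of the median paired change with its 95% confidence interval would be a useful addition, but the correction does not depend on it.

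The cost is one word. The sample size, data collection and patient burden do not change. Trial status describes recruitment as still in progress, so the correction can be made before analysis.

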### Secondary endpoints

(1)Incidence rate of all-cause mortality;(2)Incidence rate of cardiac-related mortality;(3)Incidence rate of nonfatal myocardial infarction;(4)Incidence rate of nonfatal stroke;(5)Incidence rate of repeat revascularization procedures;(6)Cardiac function indicators, including LVEF, LVESD, LVEDD, 6-minute walk test (6MWT), and brain natriuretic peptide (BNP) levels;(7)Quality of life scores;(8)Mental health scores, including anxiety scores and depression scores;(9)Biochemical indicators.

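### The named between-group tests for the continuous secondary endpoints do not adjust for the outcome's baseline value, which costs precision that data already scheduled could recover

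*Protocol article*

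**What the plan says.** The Secondary endpoints section lists "Cardiac function indicators, including LVEF, LVESD, LVEDD, 6-minute walk test (6MWT), and brain natriuretic peptide (BNP) levels", together with quality of life, anxiety and depression scores and biochemistry.

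The Statistical analysis section, under statistical inference, fixes the methods:

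- Between groups: "normally distributed continuous variables will be analysed via independent sample *t* tests". Otherwise: "For nonnormally distributed continuous variables, comparisons will be performed via the Mann–Whitney *U* test".
- Over time: "repeated-measures ANOVA will be used to assess between-group differences over time".
- Within groups: "Within-group comparisons involving continuous variables with a normal distribution will utilize paired *t* tests", with a rank test if the data are not normal.
- Adjustment: "Further analyses will include multivariate model adjustments to account for potential confounding factors and to determine the stability of the results". No covariates are listed.

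The only step on missing data compares the baseline characteristics of patients who are and are not in the final analysis. An effect estimate with a confidence interval is promised for the primary endpoint only.

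Table 5 marks all these measures at baseline and at 30, 90, 180 and 365 days. The Study procedures section stratifies randomisation by GRACE category and centre.

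**The concern.** Most of these outcomes vary widely between patients and are likely to track within a patient. A comparison of follow-up values that leaves the baseline out carries all the between-patient variation into the standard error. Putting the baseline value in the model removes part of that variation at no cost in data, and it is standard practice in a randomised trial.

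Two further weaknesses come from the same text. Because a normality check chooses the method, it is not settled in advance whether the reported effect for a given endpoint is a difference in means or a rank comparison; this matters most for BNP, which is likely to be skewed. In addition, no method is named that keeps a patient with some visits missing. The classical form of repeated-measures ANOVA needs complete rows, and patients with complete rows may be the healthier ones.

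At stake are the precision and clarity of the secondary results, not the primary conclusion.

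**Working it through.** **The plan's own figure.** The article gives no calculation for the secondary endpoints. Its sample size is for MACCE: n = 2 × 0.17 × 0.83 × (1.96 + 0.84)² / (0.20 − 0.14)² = 614.6, so 615 per group and 1,230 in total; 1,230 / 0.9 = 1,366.7, which agrees with the stated 1,366 up to rounding. This point does not alter it. I use 615 per arm below as the evaluable number.

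**Assumed inputs.** The article gives neither the baseline–follow-up correlation r nor the share m of measurements missing per visit. I take r = 0.3 to 0.7 and m = 2% to 10%, with missingness independent between visits.

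**1. Baseline adjustment at one visit.** The variance of the adjusted difference, relative to a t test on the follow-up value, is 1 − r². With 615 per arm the t test detects (1.96 + 0.84) × √(2/615) = 0.160 SD with 80% power. Power for that same difference after adjustment:

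| r | 1 − r² | Variance saved | Power |
|---|---|---|---|
| 0.3 | 0.91 | 9% | 83.6% |
| 0.5 | 0.75 | 25% | 89.9% |
| 0.7 | 0.51 | 49% | 97.5% |

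**2. Does entering baseline as a time level in the ANOVA recover this?** Take baseline plus four visits, unit variance and equal correlation r between all time points.

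- Baseline-adjusted mean of the four follow-ups: variance (1 + 3r)/4 − r².
- Group main effect over all five time points: variance (1 + 4r)/5. A constant post-baseline effect is diluted to 4/5, so the comparable variance is that divided by 0.8².
- Mean follow-up minus baseline, the contrast within the arm-by-time term that uses baseline most directly: variance (1 + 3r)/4 + 1 − 2r.

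| r | Adjusted | Main effect | Change | Adjusted / main effect | Adjusted / change |
|---|---|---|---|---|---|
| 0.3 | 0.385 | 0.6875 | 0.875 | 0.56 | 0.44 |
| 0.5 | 0.375 | 0.9375 | 0.625 | 0.40 | 0.60 |
| 0.7 | 0.285 | 1.1875 | 0.375 | 0.24 | 0.76 |

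Under these assumptions, using baseline as a level does not match using it as a covariate.

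**3. Complete cases, only if the ANOVA is listwise.** The share with all k follow-up measurements is (1 − m)^k, or 0.9 × (1 − m)^k after the dropout allowance ("With a potential 10% dropout rate considered").

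| m | k = 4 | Of 1,366 | k = 4 after dropout | k = 2 after dropout |
|---|---|---|---|---|
| 2% | 92% | 1,260 | 83% | 86% |
| 5% | 81% | 1,113 | 73% | 81% |
| 10% | 66% | 896 | 59% | 73% |

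The k = 2 column is relevant because Table 4 schedules fewer measurements than Table 5.

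**4. The schedule.** Three parts of the article disagree:

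- Table 5 has baseline and four follow-ups, with every measure at each.
- Table 4 has LVEF at baseline, 3 and 12 months; 6MWT at baseline, 1 and 12 months; BNP at baseline and 1 month; and SF-36 and HADS at 3 and 12 months with no baseline. It makes month 6 a phone call and does not list LVESD or LVEDD.
- Table 3 and the text around it have five visits, including month 9.

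**The case against.** A reader might infer that the plan throws away the baselines it collects. The article does not say so. Baseline can enter the repeated-measures ANOVA as a time level, it can be used in the paired within-group tests, and the unspecified multivariate adjustment could include it. What can be said is only that no baseline covariate is named for the between-group comparisons.

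A reader might also infer that every patient with one missed visit is lost. No listwise rule is stated. A t or Mann–Whitney test at a visit uses everyone measured at that visit, and the handling of missing visits is something an article may leave to an analysis plan that is not shown. The retention figures are therefore conditional on classical ANOVA and on the assumed missingness.

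Three more points are fair. Omitting the baseline does not bias a randomised comparison; it costs efficiency, and 615 per arm already detects 0.16 SD. A Mann–Whitney test can be accompanied by an estimate such as Hodges–Lehmann. And if Table 4 is the true schedule, there is no baseline SF-36 or HADS to adjust for.

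What remains is that the article does not leave the choice open. It names the unadjusted tests, puts adjustment among further analyses meant to check stability, and lets a normality check choose the effect measure.

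**Conclusion.** The point holds as an efficiency and prespecification weakness confined to the continuous secondary endpoints. The named between-group analyses do not use the outcome's baseline as a covariate. Adjustment would reduce the variance by about 9% to 49% against a follow-up-only comparison if r lies between 0.3 and 0.7; both limits are assumptions. The possible loss of patients, down to about 92% to 66% over four visits before dropout, arises only if the ANOVA is run listwise with 2% to 10% independent missingness per visit. No bias from the missing adjustment is claimed. The change is worth making because it costs little, but no endpoint is made invalid without it.

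**What to change.** 1. First reconcile Table 4, Table 5 and the five-visit text: which measures are taken at which visits, and whether SF-36 and HADS are collected at baseline.
2. Make the main between-group analysis of each continuous secondary endpoint a mixed model for repeated measures with baseline value, arm, visit, arm × visit, GRACE category and centre, using all observed visits. ANCOVA at 12 months with the same covariates is an acceptable simpler choice. Report the adjusted 12-month difference with its 95% confidence interval.
3. Analyse BNP on the log scale and report a ratio of geometric means. Fix this in advance, drop the normality check as the selector, and keep the rank tests as sensitivity analyses.
4. State that estimates after death are model-based, and report deaths by arm alongside.

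The cost is wording in the analysis plan and standard software. If Table 5 describes what is collected, no further data are needed. If Table 4 does, SF-36 and HADS have no baseline value to enter and BNP has no 12-month value, so the model and the reported time point for those endpoints must be set to match. The Trial status section says recruitment is still under way, so the change can be written down before the analysis.

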### Study procedures

This study will adopt a stratified block randomization approach.
(1)First, patients will be stratified based on their GRACE scores.For GRACE scores, with respect to the postdischarge patients, the low-risk category will consist of patients with scores up to 88, the moderate-risk category will consist of those scoring between 89 and 118, and the high-risk category will consist of patients scoring greater than 118. Patients in the low-risk category will have a score of 108 or less, those in the moderate-risk category will have scores ranging from 109–140, and patients in the high-risk category will have scores greater than 140.
Randomization will be stratified by GRACE risk score (low, moderate, high) and center. Blocks of 4 patients within each stratum will be randomized 1:1 using a web-based system (Sealed Envelope™), ensuring allocation concealment.(2) Block randomization within strataRandomization within strata will be achieved via block randomization as follows.
(1)Numbering: Patients will be numbered on the basis of the order of their enrolment within each stratum. For example, the first high-risk patient will be labelled H001, the first moderate-risk patient will be labelled M001, and the first low-risk patient will be labelled L001, thereby generating continuous ID numbers within each stratum.(2)Block formation: Every four consecutively enrolled patients within each stratum will be grouped into one block; thus, each block will include four patients.(3)Randomization: A seed number will be established, and four random numbers corresponding to the IDs will be generated within each block. The four subjects within each block will then be ranked according to the random numbers. The top two subjects in each block will be assigned to the experimental group, whereas the bottom two subjects will be assigned to the control group. The allocation results will be sorted in ascending order by ID number to form a randomization table within each stratum.
(3)Patient groupingResearchers at each centre will obtain randomization information for patients from a designated person based on the randomization table and the order of patient enrolment. The participants will be equally divided between the experimental group and the control group.

Experimental Group: Within one year after discharge, patients will receive digital platform management in addition to the current standard postoperative follow-up management.

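### Randomisation is stratified by GRACE risk and centre, but the analyses named for MACCE do not carry these factors and none is designated as confirmatory; the cost is small and the fix is a matter of wording

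*Protocol article*

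**What the plan says.** **Design.** Under Study procedures: "Randomization will be stratified by GRACE risk score (low, moderate, high) and center". Blocks are of four, allocation is 1:1 and there are nine centres, so there are up to 3 × 9 = 27 strata. The same section gives two sets of GRACE limits: 88 and 118, introduced for patients after discharge, and 108 and 140, with no label. It does not say which set defines the strata.

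**Sizing.** The primary endpoint is the incidence of MACCE within one year of discharge. The sample size section compares two proportions, 20% in the control group and 14% in the experimental group: "In this study, *α* = 0.05 and *β* = 0.2 were chosen".

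**Analysis.** The Statistical analysis section offers three routes to MACCE:
- chi-square, Fisher or rank-sum tests for categorical variables in general, without naming MACCE;
- Kaplan–Meier curves for cardiovascular events, where "log-rank tests will be used for comparisons";
- Cox regression, the only method tied by name to the primary endpoint: "Cox proportional hazards models will be used to estimate the hazard ratio (HR) and 95% confidence interval (CI) for the primary endpoint".

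On covariates it says: "Further analyses will include multivariate model adjustments to account for potential confounding factors". GRACE and centre are not mentioned in this section, and no route is called primary or confirmatory.

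**The concern.** Stratified randomisation forces the arms to be balanced on GRACE category and centre. If those factors predict MACCE, the treatment comparison varies less from trial to trial than an analysis that ignores them assumes. Its standard error is then too large, the test rejects less often than 5% under the null, and some precision created by the design goes unused.

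The plan places adjustment among later checks and justifies it by confounding. That is not the reason for carrying stratification factors into a randomised comparison. The reason is that the analysis should match how patients were allocated.

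The second half of the point is that nothing says which result decides the trial. The sample size rests on a difference in proportions, while the only estimate named for the primary endpoint is a hazard ratio. A one-year proportion and a time-to-event analysis also treat patients lost before one year differently, and the plan allows for 10% dropout. The routes can therefore differ in who contributes as well as in method.

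**Working it through.** **1. The plan's own figure.** Inputs from the sample size section: p1 = 0.14, p2 = 0.20, mean 0.17, Z values 1.96 and 0.84.

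n = 2 × 0.17 × 0.83 × (1.96 + 0.84)² / 0.06² = 614.6, so 615 per group. This reproduces the stated figure. The formula has no strata in it.

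**2. Assumed strata.** The article gives no MACCE risk by GRACE category, so these control-arm risks are assumptions, both averaging 20%:
- A: 12/20/28%, equal weights.
- B: 10/20/36%, weights 40/35/25: 0.40 × 10 + 0.35 × 20 + 0.25 × 36 = 20.

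Between-stratum variance at a mean of 20% is 0.00427 for A, from (0.08² + 0 + 0.08²)/3. For B it is 0.0104, from 0.40 × 0.10² + 0.25 × 0.16². Scaling the risks to the pooled 17% multiplies each by 0.85² = 0.7225. The share s of the total variance 0.17 × 0.83 = 0.1411 is then:
- A: 0.00308 / 0.1411 = 2.2%
- B: 0.00751 / 0.1411 = 5.3%

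**3. Type I error when the strata are ignored.** 2 × P(Z > 1.96/√(1 − s)):
- A: 1.96/0.989 = 1.982, giving 4.8%
- B: 1.96/0.973 = 2.014, giving 4.4%

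**4. Power at 615 per group.** The standardised difference is 0.06/√(2 × 0.1411/615) = 2.801.

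| | Unstratified: Φ[(2.801 − 1.96)/√(1 − s)] | Stratified: Φ[2.801/√(1 − s) − 1.96] | Gain |
|---|---|---|---|
| A | Φ(0.850) = 80.2% | Φ(0.872) = 80.8% | 0.6 points |
| B | Φ(0.864) = 80.6% | Φ(0.919) = 82.1% | 1.5 points |

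**5. Check on the log-rank scale, with centre.** The sized rates correspond to HR = ln(0.86)/ln(0.80) = 0.676. About 615 × (0.14 + 0.20) = 209 events are expected in 1,230 patients, with power 80.8% by Schoenfeld's formula. The simulation used 1,230 patients, 27 strata, blocks of four, mean control risk 20% and no loss to follow-up, with 6,000 null and 3,000 alternative runs per row. Simulation standard errors are about √(0.05 × 0.95/6000) = 0.3 points for type I error and √(0.8 × 0.2/3000) = 0.7 points for power. The strengths of the factors are again assumptions.

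| GRACE hazard ratios; SD of centre effect (log hazard) | Unstratified type I error | Stratified type I error | Unstratified power | Stratified power |
|---|---|---|---|---|
| 1/1/1; 0 | 5.1% | 5.1% | 79.9% | 79.4% |
| 1/1.5/2.5; 0.2 | 4.4% | 4.9% | 79.9% | 80.9% |
| 1/2/4; 0.4 | 3.9% | 4.8% | 78.0% | 80.3% |
| 1/3/8; 0.5 | 3.3% | 5.3% | 76.6% | 81.7% |

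**6. Choice of test.** Declaring success if either chi-square or the unstratified log-rank is significant gave a type I error of 5.4% when the strata have no effect, and 3.5% to 4.6% when they do.

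**The case against.** The strongest objection is that this is inferred from silence. A reader might conclude that the plan commits to an unstratified analysis, but the article never says stratified, unstratified or unadjusted, and a condensed article may leave model terms to an analysis plan that is not shown. That stands against the stronger wording. It does not dispose of the point, because the article does more than stay silent: it lists its tests, ties Cox to the primary endpoint and assigns adjustment to further analyses for confounding and stability. Followed as written, the lead comparison omits the factors.

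A reader might also infer three chances at p < 0.05 and hence an inflated error rate. The documents do not support that. Chi-square is only implied for MACCE, Cox is named for estimation, and in a two-arm comparison the log-rank test is essentially the Cox score test. Picking between chi-square and log-rank reached only about 5.4%.

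Nor does the plan's 80% power fail. The sizing formula ignores strata, and in the closed-form illustration the unstratified test still exceeds 80%. The simulated values of 78.0% and 76.6% need strong assumed factors for which the article gives no support. They also come from holding the within-stratum hazard ratio at 0.676, so the overall experimental risk ends somewhat above 14%. Likewise, the unadjusted hazard ratio lying nearer to 1 than the stratified one reflects a different estimand (non-collapsibility) and is not an error in the plan.

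**Conclusion.** The point holds as a modest improvement. The analyses named for MACCE do not carry the randomisation factors, and no single test or effect measure is designated, although sizing is on proportions and the named estimate is a hazard ratio. Omitting the factors errs on the conservative side: type I error is about 4.8% to 4.4%, and 0.6 to 1.5 points of power are forgone under the assumed GRACE risks. With centre added and much stronger assumed effects, the gap reaches about 5 points (76.6% against 81.7%). If the factors do not predict MACCE, there is nothing to gain. All these sizes rest on assumed stratum risks, weights and centre effects. No stated figure is wrong, and false positives are not materially inflated. The change is worth making because it costs almost nothing and settles which result decides the trial while recruitment is still under way.

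**What to change.** 1. Name one primary analysis of one-year MACCE: a two-sided log-rank test stratified by the randomisation factors, GRACE category and centre, with the hazard ratio and 95% CI from the matching stratified Cox model. Label the unstratified Cox and chi-square results as sensitivity analyses.
2. If sparse centres are a concern, fix a rule in advance that does not depend on outcome by arm, such as pooling centres below a stated size. The average is about 209/27 = 7.7 events per stratum in 1,230 patients, or 0.17 × 1,366/27 = 8.6 with no dropout. Centre sizes will vary, so some strata will hold fewer.
3. Reconcile the two sets of GRACE cut-points under Study procedures, so that the strata analysed are those used at randomisation.

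**Cost:** wording in the protocol or analysis plan. Sample size stays at 615 per group before dropout, and GRACE and centre are already recorded at randomisation. The small downside is that very small strata contribute little information.
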